### Data analysis

Data will be collected from the sleep report generated from the Sleep Consultant™ software, sleep diary, and questionnaires (initial and end of study). Sleep parameters measurement, i.e. sleep efficiency percentage (SE%), total sleep time (TST), sleep onset latency (SOL) and number of nocturnal awakenings (NWAK) of a single participant through either the sleep diary or actigraphy will be averaged from all the data recorded during the 2-week period (recorded as ‘pre’ (week 1) and ‘post’ (week 2) mean scores). There will be no discrimination between weekdays and weekend data. Sleep scale scores to assess sleep health using ESS, ISI, MAPI and IRLSSG survey recorded at baseline and week 2 will be averaged to mean scores for analysis.

Data will be analysed using SPSS 20.0 for windows [53]. This study will consider alpha level of 0.05 for all statistical tests. Using descriptive, paired *t*-test and independent *t*-test – demographic characteristics and sleep scale scores between and within groups will be compared. In the ICG, pairwise differences of sleep parameters mean scores between actigraphy and sleep diary will be calculated using independent *t*-test, and will be used paired-*t*-test in comparing within group, for pre– and post–mean scores (for normally distributed data). To determine correlation between two variables, Pearson’s correlation will be applied. Likert-type questions will be analysed as descriptive analysis.

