**Eligibility criteria**	
**Inclusion**	**Exclusion**
• Aged ≥ 18 years old	• Aged < 18 years old
• Attend a participating pharmacy as a ‘walk-in customer’ seeking help for sleep-related disorders or having symptoms of sleep disorders.	• Not able to speak, read and write in English, or not fluent in English and cannot arrange for a translator themselves or a translator is not available.
	• Unable to complete the screening (in the pharmacist’s opinion).
	• Refuse to give consent.
	• Pregnant.
	• Currently under treatment with continuous positive airway pressure (CPAP)

The actigraph is a useful device for monitoring sleep-related disorders, but literature suggests that it should be used in conjunction with other parameters, such as sleep diaries [31,42] as both may complement each other by providing objective and subjective data, respectively. Therefore, participants will be provided with an intervention package, which includes:

1. An actigraph (SBV2 Readiband™) to be worn 24-hours a day for seven days before participants revisit the pharmacy for their first follow-up, and then for a further seven days after the first follow-up before returning to the pharmacy for final assessment.

2. A sleep diary [43] to self-record 14 days of bedtime, wake time, time to fall asleep, number of nocturnal awakenings and total sleep time, plus information related to sleep-hygiene, lifestyle and other factors that may interrupt sleep.

3. Educational information about sleep disorders, sleep health management, sleep hygiene and healthy lifestyle to improve sleep (via access link to a website: http://sleepproblemandyou.wordpress.com/ which is developed specifically for this study). The web address will be provided to each participants.

One complete study duration for a participant in the intervention group is two weeks with follow-ups at two time points; week 1 (day 8) and week 2 (day 15). At both time points, pharmacy staff will analyse the data downloaded from the actigraph using Sleep Consultant™ software to generate an on-the-spot individualise report of sleep/wake patterns and they will also assess the self-report information from the sleep diary.

##### 

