### Study measurements and outcomes

#### *Study measurements*

Assessments will be conducted at three times points – baseline, week 1 and week 2 (Table 2). At baseline upon recruitment, participants will be assisted to complete the self-administered ‘Initial Pharmacy Visit’ questionnaires, comprise of:

• Demographic and lifestyle information, which includes sleep environment, smoking, alcohol consumption and caffeinated drinks intake, modified from the validated ‘Pharmacy Tool for Assessment of Sleep Health - POTASH’ [24].

• Health-related quality of life (HRQOL) assessment using validated WHO-Five Well Being Index (version 1998) [46,47].

• Sleep health assessment using a set of survey instruments adapted from POTASH [24]: Epworth Sleepiness Scale (ESS) [48,49], Insomnia Severity Index (ISI) [50], Multivariate Apnea Prediction Index (MAPI) [51] and International Restless Legs Syndrome Study Group (IRLSSG) [52].

• Community pharmacy survey: 14 questions using a 5-point Likert-type scale from 1 (strongly disagree) to 5 (strongly agree), and one open ended question.

**Table 2 T2:** Summary of measurements and study outcomes

**Measurements**	**Instruments**	**Group**	**T0**	**T1**	**T2**	**Outcome**	
Surveys/measuring tools							
Socio-demographic and lifestyle	Questionnaire	ICG, UCG	x				2˚
Health-related quality of life ^I,E^	WHO-5 Well-being index (1998)	ICG, UCG	x		x	1˚	
Sleep scale scores ^I,E^	ESS, ISI, MAPI, IRLSSG	ICG, UCG	x		x	1˚	
Community pharmacy survey ^I^	Questionnaire	ICG, UCG	x				2˚
Close-out survey ^E^	Questionnaire	ICG, UCG			x	1˚	2˚
Sleep parameters assessment							
SE%	Actigraph only	ICG		x	x	1˚	
TST, NWAK, SOL	Actigraph and sleep	ICG		x	x	1˚	
	diary						
Other factors that may interrupt sleep	Sleep diary only	ICG		x	x	1˚	
Pharmacy survey							
Close-out survey for pharmacy	Questionnaire	Pharmacists, pharmacy staff			x		2˚

T0 = baseline, T1 = 1 week after baseline, T2 = 2 weeks after baseline.

ICG: intervention care group; UCG: usual care group.

ESS: Epworth Sleepiness Scale; ISI: Insomnia Severity Index; MAPI: Multivariate Apnea Prediction Index; IRLSSG: International Restless Legs Syndrome Study Group.

SE%: Percentage of sleep efficiency; TST: Total sleep time per-24 hour period; NWAK: Number of nocturnal awakenings; SOL: Sleep onset latency.

1˚: Primary outcome; 2˚: Secondary outcome.

I: ‘Initial Pharmacy Visit’ Questionnaires; E: ‘End of Study’ Questionnaires.

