Follow-up after one week from baseline will be conducted in the ICG only (Table 2). Assessment (pre) of sleep parameters will be obtained from the actigraph and sleep diary for these measures: (i) Sleep efficiency percentage (SE%), (ii) Total sleep time (TST) per 24-hour period (hours/day), (iii) Number of nocturnal awakenings (NWAK), and (iv) Sleep onset latency (SOL).

Follow-up at week 2 will be conducted to complete the study in both groups (Table 2). Assessment (post) of sleep parameters will be obtained from the actigraph and sleep diary, as in previous follow-up. Participants will also complete the ‘End of Study’ questionnaires, comprise of:

• HRQOL assessment using validated WHO-Five Well Being Index (version 1998).

• Sleep health assessment (consist of ESS, ISI, MAPI and IRLSSG), adapted from POTASH [24].

• A close-out survey, consisting of: (i) questionnaire on sleep-related lifestyle and behaviour changes since completing the study, (ii) self-opinion of sleep health after the study, and (iii) willingness and ability to pay if such program is offered as a service by community pharmacy.

Upon completion of the study, pharmacists and pharmacy staff will complete a self-administered questionnaire on the feasibility of the study, and opinions on the management of sleep disorders after participating in the study (Table 2).

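### Primary outcome 2a averages actigraph and diary over whatever nights each recorded, so the two weekly means can come from different nights when either record has gaps

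*Protocol article*

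**What the plan says.** The averaging rule is in the Data analysis section. Each participant's parameters, "through either the sleep diary or actigraphy will be averaged from all the data recorded during the 2-week period", become a pre (week 1) and a post (week 2) mean. The next sentence adds: "There will be no discrimination between weekdays and weekend data". Nothing there limits the actigraph-diary comparison to nights that both instruments captured.

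The comparison is outcome 2a under Study outcomes: TST, NWAK and SOL, actigraph against diary, at week 1 and week 2, in the intervention group. It is listed as primary. The Sample size section rests on the same contrast (a 20% difference in SOL and TST).

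The intervention package (section on intervention care group participants) issues both instruments together. The actigraph is "to be worn 24-hours a day for seven days before participants revisit the pharmacy for their first follow-up", then for a further seven days. The diary is used to "self-record 14 days of bedtime, wake time, time to fall asleep, number of nocturnal awakenings and total sleep time", along with sleep hygiene, lifestyle and other items.

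On the TST window, the Table 2 footnote reads "TST: Total sleep time per-24 hour period" and names no single instrument. Study measurements introduces its list, which includes 24-hour TST, with "Assessment (pre) of sleep parameters will be obtained from the actigraph and sleep diary for these measures".

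**The concern.** Outcome 2a is meant to show how far the device and the self-report differ on the same sleep. If a participant has 7 actigraph nights and 4 diary nights in a week, the rule compares a 7-night mean with a 4-night mean. Part of the resulting difference reflects which nights were recorded and not how the two instruments measured them. Because weekdays and weekends are pooled, the two means can also carry different weekday/weekend mixes.

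Gaps are foreseeable: the diary is a 14-day self-record kept at home, and the Background justifies the actigraph partly by the weakness of self-report. What is at stake is a primary outcome and the contrast on which the sample size rests.

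**Working it through.** **The plan's own figure.** The Sample size section gives 25 per group for a 20% difference, 80% power and p = 0.05. It states no SD, so 25 cannot be reproduced. Assuming a two-sided test (normal approximation), it implies a standardised difference of √(2/25) × (1.960 + 0.842) = 0.79 for two independent samples, or √(1/25) × 2.802 = 0.56 for pairs. The total follows: 50 × 1.10 = 55. The present point changes none of this; it concerns what the difference measures.

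**Complete records.** With 7 nights on each instrument in each week, both means use the same nights and the rule does no harm.

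**Random gaps.** Assume that the instruments agree perfectly on every night, that nights vary independently with SD σ, that the actigraph has 7 nights and that the diary has k. The difference between the two weekly means then has expectation 0 and SD = σ × √(1/k − 1/7). The article gives neither σ nor the number of missing nights, so a range is shown for TST (minutes):

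| Diary nights missing (k) | √(1/k − 1/7) | σ = 45 | σ = 60 | σ = 90 |
|---|---|---|---|---|
| 1 (k = 6) | 0.154 | 6.9 | 9.3 | 13.9 |
| 2 (k = 5) | 0.239 | 10.8 | 14.3 | 21.5 |
| 3 (k = 4) | 0.327 | 14.7 | 19.6 | 29.5 |

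A simulation of 200,000 weeks per cell agrees to within about 0.1 minute and shows bias of practically 0.

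**Selective gaps.** In the same simulation, if the diary is always missing on the shortest nights, the diary mean exceeds the actigraph mean by (minutes):

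| Diary nights missing | σ = 45 | σ = 60 | σ = 90 |
|---|---|---|---|
| 1 | 10.1 | 13.5 | 20.3 |
| 2 | 19.0 | 25.3 | 38.0 |
| 3 | 27.7 | 36.9 | 55.4 |

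This is a worst case and not a forecast.

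**Weekday/weekend mix.** Suppose a 7-night actigraph week has two weekend nights and the diary lacks both. The means then differ by 2/7 (29%) of the weekend-weekday difference, even with perfect agreement.

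**Scale.** At an assumed mean TST of 7 hours (420 minutes), the planned 20% is 84 minutes.

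- Random gaps: if all 25 participants had the same number of gaps, the extra standard error of the group mean difference would be 6.9/√25 = 1.4 to 29.5/√25 = 5.9 minutes. That is small for the group test. The noise matters more for individual differences and for correlations between the instruments.
- Selective gaps: 10.1/84 = 12% to 55.4/84 = 66% of the target difference. This is where the group comparison could be misled.

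**TST window.** The listed diary items are "bedtime, wake time, time to fall asleep, number of nocturnal awakenings and total sleep time". Total sleep time is an entry of its own, and the 24-hour definition is not confined to the actigraph. No listed item shows how a nap would reach the diary total. The article gives neither nap minutes nor the diary form, so no size is put on this.

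**The case against.** Three objections to the main point deserve weight.

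- The two instruments are issued together for the same 14 days and reviewed together on days 8 and 15, so by design the nights coincide. This stands: the point depends on gaps, and the article gives no data on them.
- Rules for valid nights and missing diary entries are commonly left to a fuller document. This stands for the definition of a valid night. It does not remove the point, because the article fixes a rule, namely all data recorded by either instrument, and a matching rule elsewhere would have to override it.
- The phrase about all recorded data, followed by the weekday/weekend sentence, may mean only that no days are selected out. That is a fair reading of intent, but the rule as written still produces two means on unmatched nights.

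A reader might also infer something stronger: that 24-hour actigraph sleep is being compared with a night-only diary, so that the whole comparison is not like for like. The documents do not support this. The 24-hour TST definition is applied without limiting it to the actigraph, the diary has its own total sleep time entry, its list of contents continues beyond the sleep fields, and the cited form is not shown. If both instruments are meant to cover 24 hours and a participant leaves naps out of the diary, that is a genuine disagreement of the kind the actigraph is there to reveal. The issue could in any case touch only TST: NWAK is nocturnal by definition, and no window mismatch is shown for SOL.

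**Conclusion.** The point holds for the averaging rule. As written, the actigraph and diary means in primary outcome 2a can rest on different nights whenever either record is incomplete. For TST, random gaps add a person-level SD of about 7 to 29 minutes without bias. Gaps that always fall on the shortest nights add about 10 to 55 minutes of bias. These sizes assume a night-to-night SD of 45 to 90 minutes, 1 to 3 of 7 diary nights missing, a complete actigraph record and otherwise perfect agreement; none of these inputs comes from the article. With complete records the effect is nil. No size was worked out for SOL or NWAK, though the same rule applies to them.

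On daytime sleep, only a clarification is warranted, and only for TST: a common window is nominally defined, but the listed diary items do not show how the diary meets it.

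**What to change.** For objective 2a only, state that both weekly means of TST, SOL and NWAK are computed over nights with both a valid actigraph record and a diary entry, and report the number of matched nights per participant and week. Keep all recorded actigraph nights for outcome 1c.

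Separately, state that TST in 2a covers the same window on both instruments, and how daytime sleep enters the diary total if that window is 24 hours.

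Do not recompute actigraph SOL, NWAK or TST inside diary-reported bedtimes. That would make the objective measure depend on the self-report it is meant to check, and nothing in the article shows that the software can do it.

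The cost is a sentence or two of analysis wording and some data handling. Unmatched nights drop out of 2a, so its means rest on fewer nights, and the result describes only nights on which a diary entry was made. Matching removes the artefact of unequal nights, but it cannot recover agreement on nights without a diary entry.

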#### *Study outcomes*

The primary outcomes (Table 2) of the study will be evaluated based on these three objectives:

1. To evaluate a community pharmacy-based ‘model of care’ to improve the management of sleep disorders in the community, by comparing:

a. Changes in HRQOL mean scores between and within the intervention care group (ICG) and usual care group (UCG) at baseline and week 2.

b. Changes in sleep scale mean scores – ESS, ISI, MAPI and IRLSSG, between and within the intervention care group (ICG) and usual care group (UCG) at baseline and week 2.

c. Changes in sleep parameter mean scores – sleep efficiency percentage (SE%), total sleep time (TST), number of nocturnal awakenings (NWAK) and sleep onset latency (SOL), between pre– and post–actigraphy sleep report data in the intervention care group (ICG).

2. To evaluate the role of actigraph as an objective sleep assessment instrument to monitor certain sleep disorders, by comparing:

a. Changes in sleep parameter mean scores –total sleep time (TST), number of nocturnal awakenings (NWAK) and sleep onset latency (SOL), between actigraphy and sleep diary at week 1 and week 2 in the intervention care group (ICG).

3. To evaluate the extended role of community pharmacists in managing sleep disorders in the community, by evaluating:

a. Participants’ opinions of sleep health at the end of the study.

b. Willingness and the amount able to pay if such programme is provided as a service in the community pharmacy.

Secondary outcomes (Table 2) to be evaluated are:

1. Participants’ opinions of the community pharmacy and opinions on the use of community pharmacy to seek help for sleep-related disorders.

2. Comparison between groups in sleep-related lifestyle and behaviours at week 2 follow-up.

3. Pharmacist and pharmacy staff opinions regarding the feasibility of the study and the management of sleep disorders in the community pharmacy after participating in the study.

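### Aim 1 has no lead outcome: five scales are tested between and within arms at an unadjusted 0.05, and uncontrolled pre-post change in the intervention arm counts as primary evidence

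*Protocol article*

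**What the plan says.** The Study outcomes section states that the primary outcomes "of the study will be evaluated based on these three objectives". Objective 1, which serves the effectiveness aim, has three parts:

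- **1a (WHO-5):** "Changes in HRQOL mean scores between and within the intervention care group (ICG) and usual care group (UCG) at baseline and week 2".
- **1b (four sleep scales):** "ESS, ISI, MAPI and IRLSSG, between and within the intervention care group (ICG) and usual care group (UCG) at baseline and week 2".
- **1c (SE%, TST, NWAK, SOL):** change between the pre and post "actigraphy sleep report data in the intervention care group (ICG"), with no control-arm counterpart.

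Objective 2 compares actigraphy with the sleep diary for three parameters at two weeks. Objective 3 covers participants' opinions and willingness to pay. All of these are primary, and none is singled out.

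The Data analysis section assigns paired t-tests to within-group comparisons and independent t-tests to between-group comparisons, without ranking them. It sets one level for every test: "This study will consider alpha level of 0.05 for all statistical tests".

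Table 2 also marks the row "Other factors that may interrupt sleep" as primary, although the list in the text does not name it.

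**The concern.** An effectiveness aim needs a stated answer to one question: which result decides whether the intervention worked? Here five scales share primary status, so a mixed result (say, one scale significant between arms and four not) has no defined interpretation. Each extra unadjusted between-arm test adds to the chance of a spurious finding.

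The within-arm tests raise a different and larger problem. Participants are walk-in customers with current sleep complaints, so some average improvement over two weeks is plausible whatever they receive. A paired test in the ICG picks up that improvement together with any effect of the intervention. For 1c there is no control series to subtract. For the five scales, significance in the ICG but not in the usual care group (UCG) is not a test of the difference between them, yet both within-arm results have the same primary standing as the between-arm test.

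**Working it through.** **The plan's own figures.** The article states no familywise error rate. Its Sample size section gives 25 per group for 80% power at 0.05, based on actigraphy versus diary differences in SOL and TST. No SD is given, so the 25 cannot be reproduced. It corresponds to a standardised difference of 0.81 for a two-sample t-test or 0.58 for a paired t-test. Because it concerns two instruments, it does not identify a lead effectiveness outcome either. I use n = 25 per arm below.

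**Step 1: count the primary tests (Study outcomes).**

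| Part | Between arms | Within ICG | Within UCG | Instrument comparison |
|---|---|---|---|---|
| 1a | 1 | 1 | 1 | – |
| 1b | 4 | 4 | 4 | – |
| 1c | – | 4 | – | – |
| 2a | – | – | – | 3 × 2 = 6 |
| Total | 5 | 9 | 5 | 6 |

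The sum is 5 + 9 + 5 + 6 = 25. The six instrument comparisons say nothing about effectiveness, and improvement within the UCG cannot be claimed for the intervention. That leaves 5 + 9 = 14 tests that could be read as success.

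**Step 2: error of the between-arm family.** With five independent tests at 0.05, the chance of at least one false positive is 1 − 0.95^5 = 0.226. Positive correlation between scales lowers it. Simulation with equally correlated outcomes, 25 per arm and two-sided tests (sidedness is not stated, so two-sided is assumed) gives about 23%, 19% and 14% at correlations 0, 0.5 and 0.7.

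**Step 3: what a within-ICG test shows when there is no effect.** Suppose both arms improve naturally by *d* SDs of the change score. The documents give no value for *d*, so it is an assumption. The chance that one two-sided paired t-test with n = 25 is significant equals its power at *d*:

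| Natural improvement *d* | P(ICG significant), *p* | P(ICG significant, UCG not) = *p*(1 − *p*) |
|---|---|---|
| 0.3 | 0.30 | 0.21 |
| 0.4 | 0.48 | 0.25 |
| 0.5 | 0.67 | 0.22 |

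The last column is the pattern most easily mistaken for an intervention effect. It arises in roughly a fifth to a quarter of trials for each scale when the arms do not differ at all.

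**Step 4: the 14 tests together, no intervention effect.** Simulated chance of at least one two-sided p < 0.05:

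| Correlation | No natural improvement | Natural improvement 0.3 SD |
|---|---|---|
| 0 | about 47% | about 97% |
| 0.5 | about 37% | about 80% |
| 0.7 | about 28% | about 70% |

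Natural improvement common to both arms leaves the between-arm family where it was (about 18% at correlation 0.5). The large figures therefore come from the within-arm tests.

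**The case against.** Several points can fairly be made for the plan.

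- **The right contrast is already planned.** The between-arm comparison is listed for all five scales, and nowhere does the article say that any single significant result, or ICG significance without UCG significance, establishes effectiveness. This is true. What stands is that nothing gives the between-arm comparison precedence, and 1c has no between-arm version.
- **Multiplicity is often left to an analysis plan, and an article condenses.** For a mere absence of detail this would settle the matter. Here the article itself lists the primary outcomes and fixes 0.05 for every test, so the structure is stated and can be judged.
- **The size of natural improvement is unknown.** Correct. The 30 to 67% depends on an assumption, and only its direction is suggested by the recruitment of help-seeking customers.
- **Objective 3 is largely descriptive already.** Agreed; Likert-type items get no hypothesis test, and none is counted above.

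A reader might go further, multiply out all 25 tests (1 − 0.95^25 = 0.72) and infer that a positive primary result is likely with no effect at all. The documents do not support that. Six of those tests compare instruments, five are within the UCG, and independence is unrealistic. Without natural improvement, the 14 relevant tests give less than an even chance, and counting only results in the favourable direction would lower it again.

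**Conclusion.** The concern holds in a limited form. The effectiveness aim has no lead outcome, and uncontrolled within-arm change sits among the primary evidence. The familywise error of the between-arm comparisons is inflated to about 14 to 23%, which is moderate and does not make a false positive probable. The more serious weakness is the within-ICG evidence: at 0.3 to 0.5 SD of natural improvement, a single test is significant 30 to 67% of the time with no effect. These figures assume two-sided tests, 25 analysed per arm, equally correlated outcomes and, for the within-arm figures, a drift that the documents do not quantify. That a within-arm test cannot isolate the intervention effect does not depend on any of those values.

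**What to change.** State in Study outcomes and Data analysis that an effectiveness claim under aim 1 rests only on the between-arm comparison at week 2, adjusted for the baseline score. Then choose one of two routes before data are seen:

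1. Name one lead scale and test it at 0.05. The choice belongs to the investigators: eligibility is not restricted to particular sleep disorders, so no single scale is the obvious candidate.
2. Keep all five scales and apply Holm's procedure across the five between-arm tests.

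Report within-arm changes and outcome 1c as secondary or descriptive, with estimates and 95% confidence intervals and no effectiveness claim. Keep objective 2 as a separate question about instrument agreement, outside the effectiveness family. In the same edit, bring the Table 2 row on other factors into line with the list in the text; this is tidying and does not bear on the error rate.

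No extra participants or data are needed. Route 1 means fewer results may be called primary. Route 2 has a strictest step of 0.05/5 = 0.01. For illustration, at the 0.81 SD that 25 per group would imply for a two-sample test, power at that step is about 57% instead of 80%.

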Currently, in managing sleep-related disorders, community pharmacists depend on self-report from patients or on sleep diaries, if indicated. Monitoring sleep disorders is difficult without appropriate tools, education or standard measures. Determining the actual sleep problem and planning meaningful strategies can therefore be complicated without objective measures. To date, in our knowledge, most studies involving sleep disorders in community pharmacies focused on screening tools [24-26] with very few studies incorporating patient follow-up and monitoring by community pharmacists [27].

This study will use a step-wise approach designed to tackle ‘poor sleep’ in all individuals with disturbed sleep, with referral procedures in place if the problem is not resolved. We will investigate the potential extended role of the pharmacists and the development of an intervention to monitor individuals with poor sleep using a convenient and portable measuring device as an objective measure to gain feedback on sleep. A wrist-actigraph (SBV2 Readiband™) allows pharmacy staff to follow those undergoing treatment by measuring the quality and quantity of sleep, and to better characterise their sleep. While monitoring treatment is difficult if self-reporting is poor, the use of actigraphy can overcomes this challenge by providing objective, patient friendly and graphical feedback that confirms certain sleep parameters and validates the self-reported feedback. An individual actigraphy report can be used as the focus reference in patients’ consultations regarding sleep.

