**Follow-up 1** The participants will receive sleep advice and possible solutions focusing on behavioural strategies such as sleep hygiene, change of lifestyle, daily alcohol and caffeinated drinks consumption and activities before going to sleep, based on data gained from both parameters. Any requests for sleep medicine (‘Pharmacist only medicine’ or ‘Pharmacy medicine’) will follow the pharmacy’s standard practice. After this session, the participants will continue to wear the actigraph plus complete the sleep diary for another seven days.

##### 

**Follow-up 2 / end of study** Participants’ first (pre) and second (post) individual sleep reports will be compared to assess any particular improvement in their sleep condition after receiving sleep advice and possible solution during the first follow-up. Participants will also complete the ‘End of Study’ questionnaires. In certain circumstances (see the ‘Protocol to refer participant to a general practitioner’ subsection), pharmacists can recommend a GP referral for further examination.

##### 

**Protocol to refer participant to a general practitioner (GP) at the end of study** In these circumstances: (1) if the sleep efficiency percentage (SE%) is below 85% at the end of study (normal SE% for adult if measure using actigraphy is 85% and above) [41,44], and (2) if analysis of the data collected appears to indicate that he/she may be at risk of having/developing sleep-related problems and has reported symptoms such as:

• choking or suffocating during sleep

• stopping breathing when sleep

• snoring during sleep

• excessive daytime sleepiness

• difficulty falling asleep at night

• having problems waking up in the morning

• falling asleep too early at night

• waking up too early at night

• fatigue and having difficulty concentrating on daily tasks

• experiencing unpleasant sensations with an urge to move their limbs

Above symptoms may be indicative of another sleep disorders, specifically OSA, narcolepsy, a circadian rhythm disorder, restless legs syndromes or a primary mood disorder.

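### The actigraphy-versus-diary comparison (primary objective 2a) is assigned an independent t-test although both readings come from the same participants

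*Protocol article*

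**What the plan says.** The Study outcomes section lists objective 2a among the primary outcomes. Its three parameters are sleep onset latency (SOL), total sleep time (TST) and number of nocturnal awakenings (NWAK), and they are to be compared "between actigraphy and sleep diary at week 1 and week 2 in the intervention care group (ICG"). Table 2 likewise lists these parameters, by actigraph and diary, for the intervention care group (ICG) only.

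The section on intervention participants gives each ICG member both an actigraph and a diary for the same 14 days. Under Follow-up 1 it adds: "After this session, the participants will continue to wear the actigraph plus complete the sleep diary for another seven days". In Data analysis, the readings "of a single participant through either the sleep diary or actigraphy will be averaged from all the data recorded during the 2-week period", giving one pre mean (week 1) and one post mean (week 2).

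The test for the ICG is then named: "pairwise differences of sleep parameters mean scores between actigraphy and sleep diary will be calculated using independent", the word that follows being t-test. The same sentence gives the paired t-test to the pre-post comparison. The Sample size section bases its calculation on this same contrast: a 20% difference in SOL and TST between actigraphy and diary, 80% power, a p-value of 0.05 and 25 participants per study group.

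**The concern.** An independent t-test needs two unrelated samples. Here there is one sample measured twice over the same nights, and the plan itself calls the differences pairwise. A person who sleeps long by one instrument will probably sleep long by the other. The independent test counts that between-person spread as noise, although it cancels when each person's diary mean is subtracted from the same person's actigraphy mean.

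At stake are the p-values and confidence intervals of a primary-outcome comparison that also drives the sample size. Under positive correlation the intervals are too wide and real differences between device and diary are missed more often than they need be.

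**Working it through.** **Inputs.** From the article: 25 participants per group, alpha 0.05, 80% power, a 20% difference, and one mean per participant, instrument and week. Assumed: two-sided testing, normal data, equal SDs for the two instruments, and a within-person correlation ρ, which the article does not give and which is therefore varied.

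**The plan's own figure.** No SD is stated, so 25 can only be solved backwards.
- Unpaired t-test, 25 per group, 80% power: standardised difference 0.81, so the SD would be 20% / 0.81 ≈ 25% of the mean.
- Paired t-test, 25 pairs, 80% power: standardised difference 0.58 on the SD of the differences, which would then be 20% / 0.58 ≈ 34% of the mean.

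Either could lie behind the 25. The figure is neither confirmed nor refuted.

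**Standard error.** With n pairs and common SD σ, the true variance of the mean difference is 2σ²(1 − ρ)/n. The independent test uses 2σ²/n. Its standard error is therefore off by the factor 1/√(1 − ρ): 1.20 at ρ = 0.3, 1.41 at 0.5 and 1.83 at 0.7.

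**Interval width.** The independent test has 48 degrees of freedom (critical value 2.011) and the paired test 24 (2.064), a ratio of 0.974. The width ratio is 0.974/√(1 − ρ): 1.16, 1.38 and 1.78. The intervals are thus about 16%, 38% and 78% too wide.

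**Size and power.** Simulation, 100,000 data sets of 25 pairs per setting:

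| ρ (assumed) | True size of the independent test | Power at 0.5 SD, independent | Power at 0.5 SD, paired |
|---|---|---|---|
| −0.2 | 7% | 42% | 34% |
| 0 | 5% | 41% | 40% |
| 0.3 | 2% | 40% | 53% |
| 0.5 | 0.7% | 38% | 67% |
| 0.7 | 0.1% | 35% | 87% |

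The paired test holds 5% at every ρ. The 0.5 SD difference is illustrative and does not come from the article.

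**Power against the planned difference.** If 25 came from an unpaired calculation (0.81 SD), the independent test on 25 pairs has power of about 80%, 84%, 88% and 92% at ρ = 0, 0.3, 0.5 and 0.7. If it came from a paired calculation (0.58 SD of the differences), its power is about 70%, 53% and 25% at ρ = 0.3, 0.5 and 0.7, against the intended 80%.

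**The case against.** The best defence is that the error is confined and, under positive correlation, conservative. The Sample size section powers the study to show a difference, and an overstated standard error works against that claim. If 25 came from an unpaired calculation, the planned 80% is kept. All correlations are assumed, and at zero the test is sound. Objectives 1a to 1c do not use this comparison, and the pre-post comparison is correctly paired. All of this stands, but it limits the damage without making the test right. No other part of the article corrects the sentence.

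A reader might infer more, in four ways that the article does not support.
- **Pearson.** The article says only "To determine correlation between two variables, Pearson’s correlation will be applied". It does not tie this to actigraphy versus diary, and Pearson's coefficient is valid on paired data, so it adds no error in the standard errors.
- **A favourable error.** The Background says actigraphy "confirms certain sleep parameters and validates the self-reported feedback", so a missed difference could be misread as validation. But objective 2a is worded as a comparison of means, and nowhere is a non-significant result to be read as agreement.
- **Pooling of weeks.** Week 1 and week 2 means are recorded and compared separately.
- **Missing agreement statistics.** A condensed article may leave limits of agreement to a fuller document, so their absence is no finding.

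**Conclusion.** The point holds as an explicit error: the named test does not fit the data structure that the article itself describes, in a primary-outcome comparison. Its standard error is wrong unless the within-person correlation is zero. Positive correlation is the natural expectation when both instruments record the same nights, and the test is then conservative and inefficient. At negative correlation it is anti-conservative.

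The sizes above rest on the assumed correlations, equal SDs and 25 complete pairs. A loss of power against the planned 80% cannot be claimed outright, because it depends on which calculation produced the 25. The error reaches objective 2a only.

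**What to change.** In Data analysis, replace the independent t-test for the device-diary comparison with a paired t-test and 95% confidence interval on within-person differences (actigraphy minus diary) for TST, NWAK and SOL, done separately for week 1 and week 2. State in Sample size whether the 25 assumed paired or unpaired data, and give the SD used.

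Two additions are suggested and are not part of the error. Bland-Altman limits of agreement from the same differences would speak to the Background's claim about validating self-report. Week 1 can be read as the cleaner comparison, because participants are advised from their actigraphy and diary data at the first follow-up and week 2 diary entries come after that.

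The cost is a few words in the analysis section. No new data or participants are needed.
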